### **Study design**

This study will be randomized control trial where the participants will be randomly assigned to the Heartfulness meditation group (Intervention group) or the Gratitude practice group (Control group). All participants will be requested to fill out professional quality of life (ProQOL) survey and the “Participants’ Details” (including age, gender, work designation, years of experience, level of education, primary patient population etc.) forms before randomization. Participants will be subjected to computerized randomization to intervention group or Heartfulness meditation group and control group or the Gratitude practice group. All participants were requested to complete the professional quality of life (ProQOL) and , Work engagement scale at the baseline and at the end of 6-weeks, which will complete the first phase of the study.

If equal or more than 20 participants are willing to participate, we will continue with a second phase of the study where the trainer guided Heartfulness program will continue for six months to assess the long-term impact of Heartfulness practice on compassion fatigue and burnout. Email communication will be sent to all participants at the end of 6 weeks, asking for voluntary participation. Participants who volunteer for the second phase of the study will be asked to complete a same survey at three months and six months. Participants in Gratitude practice group will also be asked to complete the survey at three and six months after completion of study.

All participants in both groups will be provided with information, including recorded video presentations for Heartfulness meditation practice and the Gratitude practice, at the end of 6 weeks.

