## **Measure**

The Professional Quality of Life Scale-5 (ProQOL-5) will be used to determine the risk for Compassion Fatigue (CF). ProQOL-5 uses 30 questions discretely separated into three subscales, assessing Compassion satisfaction (CS), Burn out (BO), and secondary traumatic stress (STS). The reliability of the ProQOL-5 is well documented and has established its reliability with previous research reporting a Cronbach's  $\alpha$  score ranging from 0.71 to 0.88. Cutoff scores of less than 43 (mild for STS/BO, severe for CS), 43 to 57 (moderate), and 57 or more (severe for STS/BO, mild for CS) were used for analysis. Cutoff scores for each participant will be calculated, and these scores will then be used to create risk profiles that show potential CF trends. Permission to use ProQOL-5 is obtained.

The Utrecht Work Engagement Scale (UWES) assesses levels of energy and mental resilience while working, along with a sense of significance, inspiration, pride, challenge, and concentration in work. Schaufeli and colleagues (2002) first proposed the UWES as a 17-item scale. Using exploratory factor analysis, they found three distinct factors of employee engagement: vigor, absorption, and dedication, consistent with their conceptualization.

All participants will be requested to provide testimonials or descriptive answers to the following qualitative questions in writing as a part of the survey at the end of 6 weeks, 3 months, and 6 months.

- Please describe how Heartfulness meditation or the Gratitude practice has impacted your general wellbeing (stress level, sleep quality)?
- Please describe changes in your interactions with family, friends, patients, or co-workers after joining the Heartfulness meditation program or the Gratitude practice program, i.e., feeling calmer, more empathetic, or compassionate, taking more time before reacting to a situation etc.
- Please describe if Heartfulness or the Gratitude practice has impacted your professional life in any way, i.e., better communication with patients or their family, improved focus on the assignment, less fatigue etc.
- Would you like to continue Heartfulness meditation practice or the Gratitude practice after the program ends?
- Please describe some of the challenges or difficulties faced to incorporate Heartfulness practice or the Gratitude practice in your daily routine and what were some ways you were or were not able to overcome them?

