- Please suggest some ideas or feedback to improve or modify similar programs in future
- Please describe how you foresee Heartfulness practice or the Gratitude practice to be beneficial to you in future?
- How likely is it that you would recommend Heartfulness meditation practice or the Gratitude practice to a friend or family member? [Rated on a scale of 0-10; 0 - not at all likely through 10 extremely likely]

These data will be used for qualitative statistical analysis which will provide additional perspective to study results.

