### Gratitude practice group

All participants in the Gratitude practice group will be invited for an orientation session on the aspects of the study and review of the toolkit for cultivating the practice of gratitude in nursing. This program created by the American Nurses Foundation and the Greater Good Science Center (GGSC) at the University of California, Berkeley, is designed to support nurses' social and emotional wellbeing. This toolkit is based on scientific research revealing the many benefits of gratitude. This toolkit provides different ways for individuals to express gratitude during their daily interactions and work environment, such as writing a gratitude letter, taking a savoring walk, a few minutes before and after each patient encounter, during staff huddle, etc. Participants would have an opportunity to participate in a 21-days gratitude challenge by registering on [www.Thnx.org](http://www.Thnx.org) if offered during the study period. All participants will be sent an email once a week during the study period to provide a gentle reminder to practice gratitude. Participants will be asked to attend an orientation session via Zoom about Gratitude Science for 1 hour. If the participant cannot attend the meeting, they can review the recorded video for information. Participants will be provided with information to access podcast each week on gratitude practice during the 6-week study period. Tool kit available at: [https://ggsc.berkeley.edu/gratitudeforurses?\\_ga=2.59198189.1166833940.1621437217-1764624032.1620078854](https://ggsc.berkeley.edu/gratitudeforurses?_ga=2.59198189.1166833940.1621437217-1764624032.1620078854). Subjects in the control group will also complete the ProQOL-5 at the beginning and end of the six weeks and after 3 & 6 months unless they start practicing Heartfulness meditation.

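### At 3 and 6 months the 0-10 recommendation rating and the open items do not record which practice is being rated, although both arms have by then been given material on both

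*Protocol*

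**What the plan says.** The protocol's Measure section lists eight items for all participants, to be answered "in writing as a part of the survey at the end of 6 weeks, 3 months, and 6 months". Seven of them name the two practices together. The first open item begins "Please describe how Heartfulness meditation or the Gratitude practice has impacted your general wellbeing", and the closing item, scored 0 to 10, reads "How likely is it that you would recommend Heartfulness meditation practice or the Gratitude practice to a friend or family member". Only the item asking for ideas to improve future programmes names neither practice. No instruction tells the participant to answer for the assigned practice. The section says the answers will add perspective to the study results.

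Three other statements bear on how the later answers can be read:

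- Study design: both groups receive material "including recorded video presentations for Heartfulness meditation practice and the Gratitude practice, at the end of 6 weeks".
- Study design, on later follow-up of controls: "Participants in Gratitude practice group will also be asked to complete the survey at three and six months after completion of study".
- Gratitude practice group, on the same follow-up: controls complete the ProQOL-5 at the start, at the end of the six weeks and "after 3 & 6 months unless they start practicing Heartfulness meditation".

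Measurement of participation asks how often participants practised, but only at the end of 6 weeks and only about the practice of the participant's own group.

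**The concern.** A single rating that names two practices can be interpreted only if the respondent has met one of them, or if something else in the record shows which one was meant. The first condition is met during the six-week programme. After week 6 it may not be, because everyone has been given material on both. A control who answers 9 at month 3 may be recommending Gratitude, Heartfulness or both. A Heartfulness participant who has tried the gratitude toolkit raises the same question in reverse.

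At stake is the acceptability information. The recommendation item is the only numeric acceptability rating the protocol describes, and Intended Use of Research says that one or both programmes may prove of benefit to healthcare organisations. A rating that cannot be tied to a programme says little on that. The item wording is fixed in the protocol, and an analysis plan could not restore a missing reference.

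**Working it through.** The protocol states no figure on this point, so there is nothing to reproduce. The check sets its statements side by side for each survey round.

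**Week 6.** Each arm has been given only its own programme. Research Materials, Records and Confidentiality says that assessment forms carry a survey identification number, so an answer can be linked to the randomised arm and through it to a practice. One condition applies. The week-6 survey and the release of the cross-arm material are both set for the end of 6 weeks, and the order is not stated. Attribution holds if the survey comes first.

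**Months 3 and 6.** The link to the arm remains, but the link from arm to practice weakens:

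1. Both arms now hold information and videos on both practices (Study design).
2. The email seeking volunteers for the second phase, a trainer-guided Heartfulness programme, goes to all participants (Study design). Heartfulness meditation group speaks instead of those willing to continue in that arm. Whether controls may join is unclear.
3. No practice-use question is stated after week 6. Attendance records cover virtual sessions only, so home use of the videos would not appear in them.
4. The item itself does not ask which practice is meant.

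**Does the exception for controls remove the problem?** Gratitude practice group ends later follow-up for controls who start Heartfulness, but it names only the ProQOL-5. Study design asks the Gratitude group for the survey at the later visits with no exception, so the two sections conflict. There is also no counterpart for Heartfulness participants who take up Gratitude. The exception narrows the ambiguity at most in one direction.

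**Size.** The protocol gives no rating means and no rates of cross-use, so only an assumed illustration is possible. Let H and G be the mean ratings of the two practices, p the share of controls who rate Heartfulness and q the share of the Heartfulness arm who rate Gratitude. Suppose the ratings of each practice do not depend on arm. Then:

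- control mean = (1 - p)G + pH
- Heartfulness-arm mean = (1 - q)H + qG
- difference = (1 - p - q)(H - G)

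With assumed values H = 8, G = 6 and q = 0:

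- p = 0: difference 8 - 6 = 2.0
- p = 0.3: control mean 0.7 × 6 + 0.3 × 8 = 6.6, difference 1.4
- p = 0.5: control mean 0.5 × 6 + 0.5 × 8 = 7.0, difference 1.0

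These figures are not estimates for this trial. They show that the result depends on p and q, which the survey as described does not record.

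**The case against.** The strongest reply is that the joint wording is one template serving two arms. Each participant joins one programme, and Measurement of participation already has separate questions for each arm, so the protocol does distinguish them. Nothing shows that the Qualtrics form will display both names to everyone. This reply stands for week 6. For the later rounds it would succeed only if the form named the assigned practice alone, which the protocol does not say.

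A second reply is that controls who start Heartfulness leave follow-up, so a control rating Heartfulness at month 3 is largely hypothetical. If the open items count as part of the same survey as the ProQOL-5, this has some force. It does not settle the matter, because Study design states no such exception and nothing covers cross-use in the other direction.

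Third, written answers given beside the rating may name the practice. That is true of some answers, but nothing requires it, and the number on its own cannot show it.

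Fourth, no between-arm comparison of this rating is stated. Data to be utilized ties regression and repeated measures ANOVA to work engagement, compassion fatigue and burnout. This stands and limits the consequence: the dilution above would arise only if someone compared the ratings by arm.

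A reader might also infer that by month 3 everyone practises both. The protocol supports only that everyone is given information on both. Uptake is unknown, and the guided sessions that continue are Heartfulness sessions only.

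**Conclusion.** The point holds for months 3 and 6, as a low-cost improvement. At those visits the rating and the open items that name both practices cannot be reliably tied to one practice, and no stated question resolves this. Two of the three rounds of the rating are affected.

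A reader might infer that the answers can never be attributed. The documents do not support that, because at week 6 the arm identifies the practice, given survey completion before release of the cross-arm material. Nor do they support any inference that the trial's main results are at risk: the items are supplementary, and neither the ProQOL nor the UWES results depend on them.

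The conclusion assumes that the items are shown as worded in the protocol and that at least some participants use the other practice after week 6. How many would do so is not known, so the practical size of the ambiguity cannot be stated.

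**What to change.** - At months 3 and 6, ask separately about the assigned practice and the other practice, with a not-tried option for the latter and a 0-10 rating for each. This also records use of both practices.
- Summarise the rating by arm on the assigned practice only, and report ratings of the other practice descriptively.
- State that the week-6 survey is completed before the cross-arm material is released.
- Reconcile Study design with Gratitude practice group on whether controls who start Heartfulness are still surveyed, and say whether the answer covers the whole survey or only the ProQOL-5. State likewise what happens to Heartfulness participants who take up Gratitude.

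The survey already runs in Qualtrics, so the cost is some set-up work and a slightly longer form at two visits. The change must be made before those rounds are collected.

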#### Measurement of participation

- Virtual sessions attendance will be recorded by investigators
- Heartfulness group: At the end of 6 weeks, participants will be asked to report frequency of home practice of meditation, rejuvenation, and relaxation before sleep (not including virtual guided sessions)
  - How many times a week have you practiced Heartfulness meditation for at least 15-20 minutes in last 6 weeks?
  - How many times a week have you practiced Heartfulness rejuvenation technique for at least 10-15 minutes in last 6 weeks?
  - How many times a week have you listened to Heartfulness relaxation audio before sleep in last 6 weeks?

- Gratitude practice group: At the end of 6 weeks, participants will be asked to report frequency of practicing Gratitude.
  - How many times a week have you practiced any techniques of the Gratitude practice in last 6 weeks?

### **Heartfulness meditation group**

All participants in the Heartfulness Meditation group will be invited for an orientation session on the aspects of the study and the structure of the meditation protocol. Participants will also be briefed about expectations during meditation sessions and will be offered the contact details of the trainer for any further questions. There will be six additional education sessions to help the participants be comfortable with the Heartfulness practice once a week during the study period, which will be recorded and made available to the participants if they were unable to attend the live sessions. They also will receive emails with links to guided relaxation for meditation, rejuvenation, and sleep, embedded in an audio file.

- Heartfulness trainer guided virtual sessions: Guided relaxation and meditation sessions lasting 20-25 minutes will be conducted by Heartfulness trainer and primary investigator [name] every morning seven days a week. Participants will be asked to attend a minimum of two morning sessions a week.
- Guided relaxation and rejuvenation sessions lasting 15-20 minutes will be Heartfulness trainer and primary investigator [name] every morning seven days a week. Participants will be asked to attend a minimum of two evening sessions a week.
- Participants will practice meditation techniques seated in a comfortable position in their chairs during an online virtual class. They may participate in the class discussion if they choose.
- After first 6-week of study period, guided sessions will be conducted 3 times a week for the study participants willing to continue with Heartfulness practice arm for total 6 months.

Details of Virtual/Video conference calls set up and protecting privacy:

- All the sessions will be prearranged with Zoom video conferences. The details of participating in the video conference will be sent out in advance.
- A designated Zoom Enterprise account will be created. All introductory educational sessions and meditation sessions will be conducted through Zoom video conferences.
- All Zoom video sessions will be password protected. Each participant will be provided with an individual meeting ID and password to their email addresses. Participant-specific meeting ID and password will not be allowed to be shared.
- All participants' names and email addresses will be verified before allowing online video meditation or teaching sessions.
- Video sessions will NOT be recorded to maintain the privacy of the participants.

- Educational sessions will be recorded in webinar mode without inclusion of participants, to be made available for participants to review later.
- Participants will be provided with an information sheet with detailed steps to join video conferences.
- Participants will be asked to enter the initials of their first and last name with their participant ID number and will be asked to keep their videos on during virtual sessions to promote friendly interaction with a trainer.
- Participants will not be allowed to share Zoom meeting identification numbers & passwords with anyone else either privately or will be allowed to post on any social media platform (included in the participants' consent form).

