### **Study Population and Recruitment Methods**

We would like to implement an adaptive recruitment strategy to recruit a higher number of participants in the intervention group expecting a high attrition rate observed in previous studies where meditation practice was employed as an intervention. We would like to recruit 200 participants in the intervention group and 100 participants in the control group. Willing volunteers will be consented to, enrolled, and data will be collected and analyzed.

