### **Inclusion and Exclusion Criteria**

Inclusion criteria:

1. Adults above 18 years of age willing to participate in the study
2. Any healthcare worker involved in direct patient care at any healthcare facility within United States

3. Requires basic knowledge of the Internet and ability to follow instructions regarding email communications as well as accessing video conferences

Exclusion criteria:

1. Individuals less than 18 years of age
2. Participants with a history of meditation practice ( $\geq 100$  hours of meditation) will be excluded from the study to avoid participant bias

Disclaimer: Any person under medical care for depression or other mental health conditions is encouraged not to participate or only participate after discussion with his/her healthcare provider so that the study participation does not interfere with current treatment.

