### **Recruitment**

This study will be open to all healthcare professionals involved in direct patient care in any healthcare institution across United States. Principal investigator and research team will provide information regarding the study to the general public through social media platforms such as Twitter, Facebook, and Instagram etc. with use of marketing flyers (Attached as a separate

document). We will also directly contact several healthcare institutes including Premier Health Network (Dayton, Ohio) previously familiar with Heartfulness offerings through personal and professional contacts to inform about the study.

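### Orientation comes only after allocation, and no written check asks whether a volunteer can accept either arm, so avoidable loss is likely to fall more heavily on the Heartfulness arm

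*Protocol*

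**What the plan says.** **Before randomisation.** In the protocol's Study design section, participants are requested to complete the ProQOL and the details form; the sentence ends "level of education, primary patient population etc.) forms before randomization". The work engagement scale is planned at baseline, and the Informed Consent section lists it among the Qualtrics responses, but neither place puts it before randomisation.

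**Eligibility.** The inclusion criterion closest to ability to take part is technical: "Requires basic knowledge of the Internet and ability to follow instructions regarding email communications as well as accessing video conferences". It does not mention availability. The Recruitment section makes the trial "open to all healthcare professionals involved in direct patient care in any healthcare institution across United States". No clock times or time zone are given for any session.

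**After allocation.** Each arm has its own orientation: "All participants in the Heartfulness Meditation group will be invited for an orientation session on the aspects of the study" and "All participants in the Gratitude practice group will be invited for an orientation session on the aspects of the study".

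**What each arm asks.** For Heartfulness, "Participants will be asked to attend a minimum of two morning sessions a week" and "Participants will be asked to attend a minimum of two evening sessions a week". The guided video sessions are not recorded; the six weekly education sessions are. The Home practice section lets audio practice replace the guided sessions at the participant's convenience. The Gratitude arm has one live hour, with a recording for those who miss it, and is otherwise self-directed.

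**Expected loss.** Study Population and Recruitment Methods plans 200 Heartfulness and 100 Gratitude participants, "expecting a high attrition rate observed in previous studies where meditation practice was employed as an intervention". It gives no rate.

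**The concern.** Someone who leaves before randomisation cannot unbalance the arms. Someone who leaves or stops taking part afterwards can. This plan places the session that explains the study after allocation, opens entry to shift workers in every US time zone, and puts the recurring live commitment on one arm. It has no written step at which a volunteer confirms that either allocation would be workable.

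The protocol foresees attrition with meditation and answers it with extra numbers. Numbers restore precision only. If those who leave are omitted from the analysis, the remaining Heartfulness participants are a more selected group than the Gratitude participants. If they stay in the analysis without having practised, the estimated effect is diluted. Some of this loss could be avoided by changing the order of steps that already exist.

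**Working it through.** **Order of events.** Set side by side, the sections give: consent; ProQOL and details form (requested); randomisation; arm-specific orientation. The position of orientation is inferred from its arm-specific content, since the protocol does not date it.

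**Inputs.** From the protocol: 200 Heartfulness and 100 Gratitude, treated here as the numbers randomised. The protocol gives no attrition rate, effect size, SD, power or alpha, so the 200:100 figure cannot be reproduced. Everything else below is assumed.

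**1. What 2:1 recruitment does.** If it were meant to leave equal numbers of completers, it would imply 1 − 100/200 = 50% loss in Heartfulness and none in Gratitude. The protocol does not say this was the intention. With all 100 Gratitude participants retained and two-sided alpha 0.05, the difference detectable with 80% power is (1.960 + 0.842) × √(1/n_H + 1/100):

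- n_H = 200: 0.343 SD
- n_H = 160 (20% lost): 0.357 SD
- n_H = 100 (50% lost): 0.396 SD

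Precision is therefore largely protected.

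**2. Bias if only completers are analysed.** Let p be retention and ρ the correlation between the tendency to stay and a good outcome. Under a normal selection model the completer mean shifts by ρ × φ(z_p)/p, and the bias is the Heartfulness shift minus the Gratitude shift. The factor φ(z_p)/p is 0.644 at p = 0.60, 0.350 at 0.80 and 0.195 at 0.90.

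- 60% against 90%: ρ = 0.3 gives 0.3 × (0.644 − 0.195) = 0.135 SD; ρ = 0.2 gives 0.090 SD.
- 80% against 90%: ρ = 0.3 gives 0.3 × (0.350 − 0.195) = 0.046 SD (from unrounded factors); ρ = 0.2 gives 0.031 SD.
- ρ = 0 gives no bias at any retention.

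The unadjusted standard error is √(1/(200p_H) + 1/(100p_G)):

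- 60% against 90%: √(1/120 + 1/90) = 0.139 SD
- 80% against 90%: √(1/160 + 1/90) = 0.132 SD

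In the worst of these cases the bias is 0.135/0.139 = 0.97 of a standard error. Sample size does not enter the bias formula, so recruiting more people shrinks the standard error and leaves the bias as it was.

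**3. Dilution if non-users stay in the analysis.** Take an assumed true effect of 0.40 SD, no benefit in non-users, all 200 and 100 analysed, and two-sided alpha 0.05. The standard error is √(1/200 + 1/100) = 0.122 SD.

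- No non-users: 0.40 SD, power 90%
- 20% non-users: 0.40 × 0.8 = 0.32 SD, power 74%
- 30% non-users: 0.40 × 0.7 = 0.28 SD, power 63%

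**The case against.** The strongest reply is the Home practice section. Morning meditation and evening rejuvenation may both be done from audio instead of the guided sessions, and the education sessions are recorded. Outcomes are online surveys, and nothing in the protocol withdraws a person who misses sessions. A reader might infer that anyone whose shifts or time zone rule out the live sessions must become a dropout or non-user. The documents do not support that. What remains is narrower: The objectives section defines the intervention as guided through a trainer, so a participant on audio alone receives less of the programme under test. The substitution also sits uneasily with the requested attendance minimum.

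Two other readings go too far. One is that the problem touches the Heartfulness arm alone: Gratitude orientation is also arm-specific, and people there may also leave on learning their allocation, so the difference is one of degree. The other is that volunteers learn of the commitment only after allocation: the consent form and flyers are not available for this review and may describe it. It can be said only that the protocol requires no confirmation.

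It is also fair to object that the magnitudes are assumed. Loss from a timetable clash may be nearly unrelated to outcome, in which case it causes little bias. Nothing shows how much attrition comes from scheduling or how much an earlier briefing would prevent. The protocol does not prescribe a completer analysis, and a statistical analysis plan may rule one out.

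Finally, making live attendance an eligibility condition would exclude people whom the Home practice section accommodates. That objection stands, and the fix below avoids such a condition.

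**Conclusion.** The point holds as a matter of degree. Orientation follows allocation, no written pre-randomisation check covers either arm's commitment, and the baseline forms are not a condition of randomisation. The recurring unrecorded live sessions fall on one arm. Loss or reduced use after allocation is therefore likely to be heavier in Heartfulness, and 200:100 recruitment does not correct what follows from it.

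The size is unknown. The 0.03 to 0.135 SD range is an illustration that rests on assumed retention (60% or 80% against 90%), assumed correlations (0.2 to 0.3) and an analysis of completers. Its direction, in favour of Heartfulness, assumes that those who stay are those who do better. The difference between the 60% and 80% cases should not be read as the benefit of the fix. If everyone is analysed, the cost is dilution instead, again of unknown size. The change is worth making because it is cheap and moves avoidable losses to where they do no harm.

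**What to change.** First reconcile the schedule text so that the commitment can be stated. The Heartfulness meditation group section places the rejuvenation sessions in the morning but asks for evening attendance, and its attendance minimum must be squared with the substitution allowed under Home practice.

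Then amend Study design, Heartfulness meditation group and Gratitude practice group:

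- Give every volunteer one identical briefing before randomisation, live or recorded, covering both arms' activities, time commitment and session times with time zone.
- Randomise only those who have completed the baseline ProQOL, work engagement scale and details form and have confirmed that they are willing and able to take part in either arm. Participation through the permitted home practice counts; live attendance is not an entry condition.
- Keep practice-specific teaching after allocation.
- Keep everyone randomised in the primary analysis.

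The cost is amendment wording and a confirmation step in Qualtrics. The orientation sessions already exist, so no staff need be added. The downside is a somewhat narrower and more committed sample. The change will not prevent all differential loss, and participants who use audio alone will still receive less trainer guidance.
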